#### Frequency and plans for auditing trial conduct {23}

The TAILOR study is monitored at all participating sites by a set monitor assigned by the LUMC. Monitoring will be performed at set intervals determined in the monitoring plan. This interval is initially set once every year, taking into consideration the recruitment status and protocol adherence. The (internal) monitor may decide to intensify the monitoring interval. Auditing upon invitation of the hospital may occur, when deemed necessary. The frequency of auditing is unknown.

#### Plans for communicating important protocol amendments to relevant parties (e.g. trial participants, ethical committees) {25}

Substantial amendments will be submitted to the medical ethical committee of the LUMC before implementation, with the exception of amendments for the immediate safety of participants. Important protocol modifications, influencing patients, will be communicated to the central and local ethics committees as appropriate.

### Dissemination plans {31a}

Collected data will not yet be made available, since recruitment is still ongoing. The results of this trial will be submitted for publication in a scientific journal. In addition, the results will be presented in the ClinicalTrials.gov database. Outcomes of this study will be shared with the scientific community, patient representatives, sponsor and patients through conferences, meetings, newsletters and other relevant media.

## Discussion

There is an unmet clinical need for the evaluation of second-line treatment in AIH. In clinical practice, rates of CR on first-line therapy are moderately low, at least initially [13, 37]. The TAILOR study is a multicentre, phase 3b, randomised, open-label clinical trial to evaluate the efficacy and safety of TAC versus MMF in patients with AIH and no CR. Reaching CR in AIH is of ultimate importance to prevent disease progression to cirrhosis, liver transplantation or liver-related mortality [4–10, 38]. The absence of complete remission 1 year after starting treatment in AIH is related to a lower liver-transplant-free survival [10]. In this trial, we aim to provide an evidence base for an improved organogram-like set-up for treating patients with AIH and incomplete CR.

This study has several potential strengths. At this moment, no registered second-line therapy for AIH exists. To our knowledge, this is the first interventional study comparing two frequently used second-line therapies (albeit off-label) for AIH. Several retrospective studies have demonstrated a beneficial effect of both treatment strategies in patients with AIH and intolerance to azathioprine or for incomplete CR [14, 17–27]. Both drugs are registered and extensively used for the prevention of graft rejection in transplant recipients. Furthermore, using the same glucocorticoid tapering schedule after CR has been reached in both study arms enables better comparison. Additionally, the TAILOR study is carried out by the Dutch Autoimmune Hepatitis Study group that cooperates very closely on both national and international levels (i.e. in the International Autoimmune Hepatitis Group (IAIHG)).

However, some important limitations of this trial must be considered. A multicentric set-up is required to reach complete recruitment. Administrative affairs may cause delays in opening study sites, limiting enrolment. After starting as a national study, an international extension of the study might be preferable. Furthermore, the open-label set-up may introduce some form of recall bias. Additionally, TAC, and especially Envarsus, is not always available at all sites. Consequently, different forms of TAC may be used throughout the study. Additionally, experience with TAC in non-transplant centres is limited. Therefore, it is possible that these study centres may be reluctant to include patients in the study. Active involvement of the coordinating investigator may encourage less experienced study sites to include participants. Lastly, recruiting hospitals are given the opportunity to refer patients to participating sites for study visits only (T0, T24, T52). This study set-up may simplify participation for patients who prefer their own treating physician.

In conclusion, this study should answer the question whether TAC or MMF is the second-line drug of choice, in combination with glucocorticoids, in case of not reaching CR on first-line therapy in AIH. The findings of this study are expected to inform the current clinical practice guidelines on the management of patients with AIH and incomplete CR to standard therapy.

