## Trial design {8}

This is a study protocol for a phase III, multicentre, open-label (i.e. non-blinded) randomised, controlled superiority trial, with parallel group assignment and 1:1 allocation. The protocol is written in accordance with the Standard Protocol Items: Recommendation for Interventional Trials (SPIRIT) guidelines [15]. Figure 1 shows a schematic diagram of the trial as the SPIRIT figure.

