### Interventions

#### Explanation for the choice of comparators {6b}

Several retrospective studies have reported on the use of TAC as a second-line therapy in autoimmune hepatitis. In several case series, TAC was given to patients unresponsive to prednisone and/or AZA. The first study of TAC in AIH was performed by van Thiel et al [16]. They studied the use of TAC for induction treatment of AIH and found a decrease in ALT in 80% of the patients. In several subsequent (relatively) small case series, TAC was given as second-line therapy for AIH, whereas remission rates differed between 20 and 92% [14, 17–22].

The use of MMF for AIH, both in case of intolerance for first-line treatment and in case of insufficient response, has been published by our group [23]. Retrospective cohort studies indicate that in AIH patients with intolerance or insufficient response on first-line therapy, with MMF complete remission can be induced in 0–22% of patients [23–25]. One study reported a remarkable proportion of 57% remission with MMF [26]. There appeared to be a difference in remission rates between patients started on MMF for intolerance to first-line treatment or for insufficient response to first-line treatment [23–25].

Both TAC and MMF are mentioned as possible second-line therapy in guidelines and literature. In one paper, CR on MMF was reported to be 22% in patients with an incomplete response, which is lower when compared to the CR rate in patients with intolerance to AZA. A cohort of treatment naïve AIH patients has also been treated successfully with MMF [27–29].

Because of a more favourable profile of adverse effects, MMF should possibly be favoured as second-line treatment for AIH, and not TAC, although it might be less effective [30]. TAC could be more effective than MMF as second-line therapy for incomplete response. However, the aforementioned studies are all retrospective cohort studies. No randomised trials for second-line therapies for AIH have been performed.

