### Sample size {14}

A sample size calculation is based on the log-rank test for comparing two groups, a follow-up of 12 months and the assumption of exponential survival times. The expected difference between groups was formulated in terms of relative risk derived from the expected cumulative incidences in the two groups according to previous literature. Papers on MMF for insufficient response in EU and North America reported 13%, 21% and 34% CR respectively, and review of the literature on TAC in adult AIH patients was also taken into account [22, 23, 25, 36]. Assuming proportions of CR at the end of follow-up of 0.22 in the MMF group and 0.53 in the TAC group with a two-sided *α* of 0.05 significance level and power of 1 − *β* = 0.8 to determine the difference in proportions of 0.31, results, in *N* = 38 patients per group. Taking into account a 10% loss to follow-up (e.g. due to side effects), this results in *N* = 43 patients per group. Thus, we aim to include a total of 86 patients.

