### Statistical methods

#### Statistical methods for primary and secondary outcomes {20a}

Intention-to-treat analysis will be used throughout the study for primary and secondary endpoints. All randomised patients will be included in the intention-to-treat analysis. CR at 12 months will be reported as percentage. A Kaplan–Meier survival analysis with log-rank test will be performed to assess the rapidity of reaching CR. Time to CR will be censored at 12 months. In the unlikely event that a subject is withdrawn from the study due to liver-related mortality or liver transplantation, a competing risk analysis according to Fine and Gray will be performed.

All parameters will be summarised by the treatment group using descriptive statistics. Mean, standard deviation, median and range will be used for continuous variables. Counts and percentages will be used for categorical variables. For normally distributed continuous variables, Student’s *T*-test will be used, for not normally distributed continuous variables Mann–Whitney *U* test will be used. For categorical variables, the chi-square test or Fisher exact test will be used. For repeated measurements, paired *T*-test and Wilcoxon signed rank test will be used where appropriate. Confounding will be tested where appropriate.

The economic evaluation comparing the MMF and TAC policies will include a trial-based cost-effectiveness analysis (1-year healthcare costs per complete biochemical remission) and a model-based cost-utility analysis (life-long societal costs per QALY, calculated from the EQ-5D-5L).

Statistical analyses will be performed with Statistical Package for Social Sciences (SPSS), version 24.0 or higher. Two-sided tests will be used and* p*-values < 0.05 will be deemed significant.

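### The drug-of-choice conclusion goes further than a superiority test sized for a 31-point gap can support if the result is non-significant, and the difference in 12-month CR proportions is not given an interval

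*Protocol article*

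**What the plan says.** The concluding paragraph of the Discussion states, without qualification, that "this study should answer the question whether TAC or MMF is the second-line drug of choice", and expects the findings to inform practice guidelines. The limitations paragraph before it covers site opening, the open-label set-up, TAC supply and site experience. It does not mention precision or how a non-significant result would be read.

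Trial design {8} describes a "controlled superiority trial, with parallel group assignment and 1:1 allocation". Sample size {14} assumes "0.22 in the MMF group and 0.53 in the TAC group with a two-sided" α of 0.05 and power of 0.8, "to determine the difference in proportions of 0.31". This gives 38 per group, and 43 per group (86 in total) after a 10% allowance for loss. No margin is given anywhere. Statistical methods {20a} sets two-sided testing at 0.05.

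The comparator rationale {6b} says, with adverse effects in mind, that "MMF should possibly be favoured as second-line treatment for AIH, and not TAC, although it might be less effective". It then adds that TAC could be more effective and that the evidence is retrospective.

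The effect scale varies between sections. Objectives {7} and the abstract's Methods paragraph name the difference in the proportion with CR at 12 months. Primary outcome, under Outcomes {12}, expresses the endpoint as a hazard ratio with 95% confidence interval. Statistical methods {20a} reports 12-month CR as a percentage, with a log-rank test for how quickly CR is reached.

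**The concern.** A question of the form 'which of two drugs is the drug of choice' has three possible trial results: TAC better, MMF better, or no significant difference. A superiority test answers it on efficacy only in the first two. In the third, the trial is informative only as far as its confidence interval reaches, and the protocol article neither says so nor plans that interval for the difference in proportions.

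This matters here because the rationale gives MMF the better adverse-effect profile and leaves its efficacy as the open question. A reader could easily take a non-significant result as a reason to prefer MMF. If TAC's true advantage is real but well below 31 points, non-significance is a likely result, and such a reading would pass an inconclusive efficacy comparison on to guidelines. The Discussion itself links failure to reach remission at one year to lower transplant-free survival, so a missed advantage would not be trivial.

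**Working it through.** **Inputs.** From Sample size {14}: CR 0.22 (MMF) and 0.53 (TAC), two-sided α 0.05, power 0.80, 38 evaluable and 43 randomised per arm. Assumptions made here: MMF stays at 0.22; TAC advantages of 10 to 25 points are illustrative, since the article names no smallest important difference; either all 43 or only 38 per arm contribute.

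**1. The plan's own figure.** Two-proportion formula with pooled variance under the null, p̄ = (0.22 + 0.53)/2 = 0.375:

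n = [1.960·√(2·0.375·0.625) + 0.842·√(0.22·0.78 + 0.53·0.47)]² / 0.31² = 37.1, so 38 per arm. Then 38/0.90 = 42.2, so 43 per arm and 86 in total. The figure is reproduced.

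The text says that the calculation is "based on the log-rank test for comparing two groups, a follow-up of 12 months and the assumption of exponential survival times". With HR = ln(0.47)/ln(0.78) = 3.04, common log-rank formulas give about 35 per arm (Schoenfeld, 26 events), 40 (exponential hazard difference) and 42 (Freedman, 31 events). These bracket 38, so the sample size is not in dispute.

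**2. Power below the planned difference.** Exact binomial enumeration of the two-sided pooled chi-square test, MMF = 0.22:

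| True TAC advantage | 38 per arm | 43 per arm |
|---|---|---|
| 10 points | 17% | 18% |
| 15 points | 31% | 34% |
| 20 points | 47% | 53% |
| 25 points | 64% | 71% |
| 31 points | 81% | 87% |

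The normal approximation gives 18%, 33%, 51%, 69% and 86% at 43 per arm.

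**3. Interval width with equal observed rates.** Wald half-width = 1.96·√(2p(1−p)/n):

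- p = 0.22: 17.5 points at 43 per arm, 18.6 at 38.
- p = 0.375: 20.5 points at 43 per arm, 21.8 at 38.

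Equal observed rates would therefore exclude a 31-point TAC benefit but not one of 15 points.

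**4. Non-significant results that lean towards TAC (43 per arm, MMF 9/43).**

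- TAC 17/43: difference 18.6 points, p = 0.060. Wald 95% CI −0.4 to +37.6; Newcombe −0.8 to +36.3. This is the largest non-significant TAC count for 9/43 on MMF.
- TAC 15/43: difference 14.0 points, p = 0.15. Wald upper limit +32.7; Newcombe +31.7.

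Both intervals still contain the planned 31 points.

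**5. What a claim of comparable efficacy would need.** The article gives no margin, so assume 10, 15 or 20 points with equal true rates p, one-sided 0.025, power 0.80 and 10% loss. Per arm, n = (1.960 + 0.842)²·2p(1−p)/margin². For p = 0.22 and a 20-point margin this is 68, or 68/0.90 = 75.6, so 76 per arm.

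| Common CR rate | 10 points | 15 points | 20 points |
|---|---|---|---|
| 0.22 | 600 | 268 | 152 |
| 0.375 | 818 | 366 | 206 |
| 0.53 | 872 | 388 | 218 |

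Every total exceeds 86.

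**The case against.** The strongest case against is that nothing operative is wrong. The objective, the design label and the target difference are correctly bounded, and the disputed sentence is closing prose that says 'should answer', not a decision rule. That a null superiority result does not prove equality is true of every such trial, and rules for reading null results often sit in an analysis plan, which is not shown here. This argues against treating the point as a design error. It does not remove the point, because the sentence is an affirmative, unqualified claim, and the section that lists limitations leaves this one out.

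Some stronger readings are tempting, and the objection defeats them:

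- **That the protocol would choose MMF on a null result.** No section says so. The rationale is hedged and reads as equipoise, so the step is one that a reader might take.
- **That the design cannot decide in either direction.** Testing is two-sided, so a significant result can favour TAC or MMF.
- **That no interval is planned.** The primary outcome does have a 95% interval, on the hazard ratio. What the text leaves out is an interval for the difference in proportions, which is the stated objective.
- **That safety, quality-of-life and cost results should be kept out of the choice.** They are prespecified secondary outcomes and can properly inform a benefit-risk judgement. They cannot supply missing evidence on efficacy.

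It is also fair that 17/43 against 9/43 is the extreme non-significant case, that equal observed rates would exclude 31 points, and that the power figures use a chi-square test while the sample size section names the log-rank test.

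**Conclusion.** The concern holds in a limited form. The unqualified drug-of-choice claim goes beyond what this design delivers when the primary result is non-significant. On the assumptions above, a true 20-point TAC advantage would be missed about half the time (47% at 43 per arm, 53% at 38). A 15-point advantage would be missed about two times in three (66% and 69%). The interval for the difference would extend about 17.5 to 20.5 points either side of zero with equal observed rates at 43 per arm, and further towards TAC if TAC is ahead.

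The stated reporting would not make this visible on the scale of the objective, since a hazard ratio and two percentages do not give the uncertainty of a difference in 12-month proportions. The sample size is not wrong, and no section commits the trial to a mistaken inference. The fault is an overstated conclusion together with an effect measure that does not match the objective.

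**What to change.** 1. In Primary outcome (Outcomes {12}) and Statistical methods {20a}, name the TAC minus MMF difference in 12-month CR proportions, with its 95% confidence interval, as the effect measure for the primary endpoint. The hazard ratio and Kaplan–Meier analysis can stay as the description of time to CR.
2. In the Discussion, limit the efficacy conclusion to whether one drug is superior for CR at 12 months. State that a non-significant result is not evidence of comparable efficacy and is to be read from that interval.
3. Say that safety, quality-of-life and cost results may inform a benefit-risk discussion but do not stand in for evidence of comparable efficacy. If the investigators want to claim that one drug is not meaningfully less effective, a justified margin must be written down before the results are known, and at 86 patients such a claim would be underpowered for the margins tried here.

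The cost is a few sentences and one interval from data already being collected, with no extra patients. The downside is a narrower claim if the result is non-significant.

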## Trial status

The trial was registered on 16–06-2021 in the European Union Drug Regulating Authorities Clinical Trials Database (#2021–003420) and on ClinicalTrials.gov (#NCT05221411, https://www.clinicaltrials.gov/study/NCT05221411). The first patient was randomised on 24–01-2022. The trial is ongoing and actively recruiting. To date, 5 patients of the 86 patients have been randomised. Expected completion of recruitment is in 2025.

## Data Availability

Patients are coded by a numeric randomisation code. Considering the ongoing nature of the study, collected data is not made publicly available. After publication of the final manuscripts, data may be available upon reasonable request. The dataset analysed during the current study and statistical code can be requested through the principal investigator of the sponsor site, as is the full protocol.

## Abbreviations

AIH: Autoimmune hepatitis
ALT: Alanine aminotransferases
AST: Aspartate aminotransferases
AUC: Area under the curve
AZA: Azathioprine
BAASIS: Basel Assessment of Adherence to immunosuppressive medIcations Scale
CR: Complete biochemical response
EASL: European Association of the Study of the Liver
eCRF: Electronic case report form
EU: European Union
eGFR: Estimated glomerular filtration rate
GMP: Good Manufacturing Practice
HIV: Human immunodeficiency virus
HrQOL: Health-related quality of life
IAIHG: International Auto Immune Hepatitis Working Group
IgG: Immunoglobulin gamma
INR: International normalised ratio
LUMC: Leiden University Medical Center
MELD: Model end-stage liver disease
MMF: Mycophenolate mofetil
NAFLD: Non-alcoholic fatty liver disease
PIF: Patient information form
PBC: Primary biliary cholangitis
PSC: Primary sclerosing cholangitis
(S)AE: (Serious) adverse events
SPIRIT: Standard protocol items: recommendation for interventional trials
TAC: Tacrolimus
TDM: Therapeutic drug monitoring
ULN: Upper limit of normal
VCTE: Vibration-controlled transient elastography
